### Safety/harms

All AEs, distinct by severity and relationship with the randomized drug, will be documented and listed. The number and percentage of AEs will be reported, per treatment arm and overall, along with the number and percentage of participants who experienced at least one AE. Moreover, the number of concomitant medications and changes from baseline in vital signs, routine biochemistry and hematology analyses, and in respiratory endpoints will be analyzed. Discrete safety endpoints will be compared using a chi-squared test. The denominator will be the safety population. Continuous safety endpoints will be compared using a *t*-test for parametric variables or the Mann–Whitney test for non-parametric variables. The assumption of normal distribution will be checked using Shapiro–Wilk’s test.

Furthermore, AEs will be described according to the different pandemic periods [18].

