### Sample size

The study was powered to assess the potential benefit of TUDCA compared with placebo on the rate of progression, as measured by the ALS-FRS-R total score. The target number of participants was determined based on the expected proportion of responders. In the original planning, based on data from the phase II study [5], a sample size of 199 subjects per arm was calculated to detect a 10% difference between arms assuming a response rate of 10% in the placebo group. This sample size provides at least 80% power with a two-sided alpha of 5%. Considering a dropout rate of 10% at 18 months, a total sample size of 440 patients was planned. Such a sample size provides 83.3% power to detect a 13% absolute difference in survival (defined as death or respiratory insufficiency) between the two treatment groups, corresponding to a hazard ratio of 0.616, assuming an 18-month survival of 60% in the placebo group. However, due to the impact of the COVID-19 outbreak on recruitment [9], the enrolment was planned to be closed at 320 randomized patients. The reassessed sample size allows us to detect an absolute difference of 11% in the proportion of responders between the TUDCA and the placebo arms. It also provides a power of 80% to detect a 14% absolute difference in survival, corresponding to a hazard ratio of 0.58.

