### Analysis population

ITT population is defined as all patients who were randomized into the study.

The per-protocol population includes those patients adherent to both visit and medication, respectively defined as patients who completed at least 80% of the expected routine study visits and consumed at least 80% of the prescribed assigned medication [10, 11].

Following the COVID-19 amendment (March 23, 2020), telemedicine visits were introduced as an alternative to in-person visits. For the per-protocol analysis purpose, these two modalities will be considered exchangeable.

The safety population (full analysis population) includes all subjects participating in the trial who received at least one dose of the trial medication. The safety population does not include subjects who dropped out before receiving any treatment.

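### Adverse events are compared between arms only as crude proportions that ignore time at risk, although the survival effect the plan is powered for would lengthen follow-up on TUDCA

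*SAP article*

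**What the plan says.** Safety/harms reports the number and percentage of AEs by arm and overall, "along with the number and percentage of participants who experienced at least one AE". For the comparison it states: "Discrete safety endpoints will be compared using a chi-squared test. The denominator will be the safety population". The Analysis population section defines that denominator as "all subjects participating in the trial who received at least one dose of the trial medication", so a patient counts as one whether observed for one month or eighteen. No person-time, exposure-adjusted or time-to-event analysis of AEs is named. The section ends: "Furthermore, AEs will be described according to the different pandemic periods".

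The Sample size section supplies the survival assumptions. Planning was done "assuming an 18-month survival of 60% in the placebo group", for a "13% absolute difference in survival (defined as death or respiratory insufficiency) between the two treatment groups" with 440 patients (hazard ratio 0.616, power 83.3%). For the reduced sample of 320 it says: "It also provides a power of 80% to detect a 14% absolute difference in survival, corresponding to a hazard ratio of 0.58".

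The plan uses time-to-event methods elsewhere: Kaplan–Meier curves for withdrawal and loss to follow-up, and Kaplan–Meier with a log-rank test for COVID-19 protocol deviations.

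**The concern.** A patient who dies early has less time in which to report an AE. If one arm survives longer, its patients collect more AEs even when the monthly AE rate is the same in both arms. The plan is powered for such a survival difference, yet its AE comparison takes no account of observation time. Long-term safety and tolerability is a stated secondary objective. A crude difference could be taken for toxicity when it reflects exposure. If survival were worse on TUDCA, the same mechanism could mask a real excess of AEs. In ALS, disease events such as respiratory failure and death may also be recorded as AEs. The crude percentage then mixes drug effects, disease events and exposure.

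**Working it through.** **Inputs from the document.** Placebo survival 60% at 18 months; TUDCA 73% (original) or 74% (reassessed); hazard ratios 0.616 and 0.58; 440 or 320 patients, 1:1; two-sided 5%.

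**Assumptions not in the document.** Constant event hazard; constant AE hazard h, equal in both arms; the share of the survival-event hazard that ends AE observation (100%, 50% or 25%).

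**1. The plan's own figures.** ln(0.73)/ln(0.60) = 0.616, as stated. ln(0.74)/ln(0.60) = 0.589, close to the stated 0.58. Events: 220 × 0.40 + 220 × 0.27 = 147.4, and 160 × 0.40 + 160 × 0.26 = 105.6. By Schoenfeld, power = Φ(√D/2 × |ln HR| − 1.96):
- D = 147.4, HR 0.616: 83.7% (stated 83.3%).
- D = 105.6, HR 0.58: 79.9% (stated 80%).

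The survival figures are sound as a basis for what follows.

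**2. Mean time at risk over 18 months.** λ = −ln(S)/18 gives 0.02838 (placebo), 0.01748 (73%) and 0.01673 (74%). Mean time = (1 − S)/λ:
- placebo: 0.40/0.02838 = 14.09 months;
- TUDCA: 15.44 (73%) or 15.54 (74%).

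Ratio 1.096 to 1.103; using HR 0.58 directly it is 1.105. Adding a common 10% dropout gives 1.094 to 1.101. Weibull shapes from 3 to 0.7 give 1.04 to 1.13.

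**3. Crude AE proportions under an identical AE rate.** p = h/(h + λ) × [1 − exp(−18(h + λ))]. At h = 0.05:
- placebo: 0.6379 × 0.7561 = 48.2%;
- TUDCA (74%): 0.7493 × 0.6991 = 52.4%.

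Chi-squared rejection with 160 per arm (normal approximation): difference 0.0416, standard error √(2 × 0.503 × 0.497/160) = 0.0559, z = 0.74. Rejection is about 11.2% in the direction of harm and 0.3% in the other.

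| Share of event hazard ending observation | Extra follow-up on TUDCA (74%) | h = 0.05: placebo v TUDCA, rejection | h = 0.08: placebo v TUDCA, rejection |
|---|---|---|---|
| 100% | 10.3% | 48.2% v 52.4%, 11.5% | 63.3% v 68.2%, 15.1% |
| 50% | 5.2% | 53.4% v 55.7%, 7.0% | 69.4% v 72.1%, 8.4% |
| 25% | 2.6% | 56.2% v 57.5%, 5.6% | 72.7% v 74.1%, 6.0% |

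For uncommon AEs (0.005 to 0.01 per month), rejection is only 5.6% to 6.3% even in the first row. Simulation of the first row gave 12.1% and 15.3% for chi-squared. A log-rank test of time to first AE, censoring at death, stayed at 5.2% to 5.4%.

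**4. The terminal event counted as an AE.** The proportion becomes 1 − exp(−18(h + λ)). With every event counted, at h = 0.05 it is 75.6% placebo v 69.9% TUDCA; at h = 0.08 it is 85.8% v 82.5%. The test then favours TUDCA in about 21% and 12% of trials, and goes against it in under 0.5%.

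**5. Pandemic periods.** Assume uniform accrual of 320 patients from 20 May 2019 to 4 April 2022 (1,050 days), and 3 February 2020 (259 days in) as the end of the pre-pandemic period. That boundary is an assumption, taken from the date of the case report form changes. Ignoring attrition, 320/1050 × 259²/2 = 10,222 patient-days, or about 336 patient-months. The total is about 160 × (14.09 + 15.54) = 4,741, so roughly 7% of exposure falls in that period.

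**The case against.** A reader might infer that an effective drug would look more harmful than placebo. The document does not support that as a general statement. Safety/harms covers all AEs and excludes none, and step 4 shows the reverse once fatal or respiratory events are counted.

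A reader might also take the 10% as the plan's own figure for follow-up. It is not. The plan gives survival free of death or respiratory insufficiency, and Table 2 includes tracheostomy and prolonged non-invasive ventilation, after which AEs can still be recorded. Under a constant hazard 10% is near the upper end, and it requires the hypothesised survival benefit to be real.

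Nor is the chi-squared test invalid whenever follow-up differs. The proportion with an AE by month 18, with death as a competing event, is a legitimate absolute risk. A cumulative incidence curve treating death that way would return the same 48.2% and 52.4% if death were the only reason for observation to end. The weakness is that this quantity does not isolate drug toxicity.

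Two further extensions fail. AEs by pandemic period are only described, with no test or risk comparison claimed. The plan also does not say whether the number of concomitant medications falls under the chi-squared or the continuous-endpoint tests.

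Finally, the article condenses a fuller SAP, and its survival and withdrawal analyses let readers see differential follow-up. That lessens the problem but does not remove it, because the article itself states the test and the denominator.

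**Conclusion.** The point holds in limited form. The stated AE comparison ignores time at risk, and the survival effect the plan is powered for would make follow-up longer on TUDCA: by up to about 10% if every survival event ends AE observation, and about 3% to 5% if a quarter to a half do. At AE rates of 0.05 to 0.08 per month unrelated to progression, the false-positive rate is about 6% to 15% instead of 5%, and the excess lies in the direction of harm. For AEs tied to progression or death the crude comparison can favour TUDCA instead. These sizes rest on a constant hazard, equal AE rates in the two arms, 160 patients per arm and a real survival benefit. The crude test is usable as a description of absolute risk, but alone it does not show drug toxicity in either direction. The matter is an inexpensive improvement to a secondary objective; the primary analysis is unaffected.

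**What to change.** In Safety/harms, keep the counts, percentages and chi-squared test as planned, and add:

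- AE rates per 100 patient-months by arm, with a rate ratio and 95% CI that allows for repeated events per patient.
- For key AE categories, a time-to-first-AE comparison (cause-specific hazard, by log-rank or Cox model), censoring at death or end of follow-up.
- Progression-related and fatal events shown separately from other AEs.
- Patient-months beside the descriptive AE counts for each pandemic period.

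Cumulative incidence with death as a competing event may be shown as the absolute risk, but it should not be presented as removing the exposure difference.

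The cost is some SAP wording and a few extra tables. It assumes that AE onset dates are recorded, which the article does not state. The Timing of final analysis section keeps the blind until all analyses are done, so while that holds the additions can be specified without knowledge of treatment and documented as supplementary.

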### Randomization

Patients are randomized 1:1 to receive TUDCA or placebo. After completing the lead-in period at month 0, eligible patients are randomized by means of a computerized central randomization system and coupled to a unique treatment code through an electronic platform. The randomization list has been generated using STATA software with the “ralloc” command. A permuted block randomization procedure, stratified by country, has been adopted to ensure balance across treatment groups.

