## Statistical principles

Statistical significance will be determined by a two-sided *p*-value ≤ 0.05. Confidence intervals at the 95% level (95% CI) will be reported for all outcomes and measures of association (proportions, means, odds ratios and hazard ratios). Main analyses will be carried out on the intention-to-treat (ITT) population.

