## Analysis

### Outcomes

The primary outcome is measured through the identification of the responder patients, defined as those showing an improvement of at least 20% in the ALSFRS-R slope during the 18-month randomization period compared to the 3-month lead-in period. Slope coefficients for ALSFRS-R decline will be calculated separately for the lead-in period and the treatment period using the linear regression model.

The secondary efficacy outcomes are presented in Table 2. The safety and tolerability of TUDCA will be evaluated through the assessment of adverse events, concomitant treatments, physical examinations, vital signs, and routine laboratory tests (hematology and biochemistry).

**Table 2 Tab2:** Secondary and exploratory outcomes

Variable	Description

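### The stated laboratory and vital-sign comparison (t-test, or Mann–Whitney after a normality check) is insensitive to large abnormal values confined to a few patients

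*SAP article*

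**What the plan says.** Safety/harms treats changes from baseline in vital signs, routine biochemistry, hematology and respiratory endpoints as quantities to be analysed. Continuous safety endpoints get a t-test if parametric, or "the Mann–Whitney test for non-parametric variables". The choice rests on one sentence: "The assumption of normal distribution will be checked using Shapiro–Wilk’s test". The section gives no level for that check and does not say whether it is applied per arm or to the pooled data.

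The same section lists adverse events by severity and relationship to the study drug. It reports, per arm, the number and percentage of events and of participants with at least one. It also plans a chi-squared test for discrete safety endpoints, which it does not define, with the safety population as denominator. The Outcomes section names laboratory tests and vital signs beside adverse events as the basis of the safety evaluation, and Study objectives makes long-term safety a secondary objective. Table 1 has safety parameters collected at every visit.

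**The concern.** A t-test and a Mann–Whitney test both ask whether one arm as a whole lies higher than the other. Toxicity may instead affect a small subset strongly and leave everyone else unchanged. The normality check then works against detection: the extreme values cause the rejection, and the rejection selects the test that discards how extreme they are. A biochemistry variable could give an unremarkable p-value although several TUDCA patients and no placebo patients had a marked rise. At stake is how informative the laboratory and vital-sign tables are for the safety objective. The primary analysis is not affected.

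**Working it through.** **Inputs from the SAP article.** Level: "Statistical significance will be determined by a two-sided" p-value of at most 0.05 (Statistical principles). Allocation: "Patients are randomized 1:1 to receive TUDCA or placebo" (Randomization). Size: "the enrolment was planned to be closed at 320 randomized patients" (Sample size), so 320/2 = 160 per arm. The 10% dropout in Sample size gives 160 × 0.9 = 144 per arm as a second setting.

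**Plan's own figure.** Safety/harms states no figure, so only the sample-size inputs can be checked. For 10% v 20% responders, n = [1.960·√(2·0.15·0.85) + 0.842·√(0.10·0.90 + 0.20·0.80)]² / 0.10² = (0.990 + 0.421)²/0.01 ≈ 199 per arm, as stated. Then 398/0.9 gives 443, against the planned 440.

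**Assumptions (none is in the document).** Placebo changes are N(0,1). A fraction f of TUDCA patients gains a rise of 5 to 7.5 SD. Shapiro–Wilk is applied at 0.05, and rejection in either arm leads to Mann–Whitney. The limit for counting is 4 SD. There were 2,000 simulated trials per setting.

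**Results, 160 per arm, no placebo patient with a rise:**

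| f | Shapiro–Wilk rejects | Plan's rule | t-test, no switch | Fisher on counts | Chi-squared on counts |
|---|---|---|---|---|---|
| 0 | 9% | 5% | 5% | 0% | 0% |
| 2% | 96% | 6% | 15% | 9% | 39% |
| 3% | 99% | 8% | 24% | 31% | 67% |
| 5% | 99.9% | 11% | 50% | 79% | 95% |
| 8% | 100% | 23% | 86% | 99% | 100% |
| 10% | 100% | 37% | 95% | 99.8% | 100% |

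**Closed-form check of the rank test.** If affected patients exceed essentially all placebo values, the probability that a TUDCA value exceeds a placebo value is 0.5 + f/2, whatever the size of the rise. Its null standard error is √[(160 + 160 + 1)/(12·160·160)] = 0.0323.
- f = 5%: z = 0.025/0.0323 = 0.77; power = Φ(0.77 − 1.96) + Φ(−0.77 − 1.96) ≈ 12%.
- f = 2%: z = 0.010/0.0323 = 0.31; power ≈ 6%.

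Both agree with the simulation and show why worse toxicity is no easier to see. With rises of 10 to 15 SD at f = 5%, the plan's rule stays at 11% while the t-test goes from 50% to 78%.

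**Variations.**
- 144 per arm, f = 5%: rule 11%, t-test 46%, Fisher 69%.
- 1% of placebo and 5% of TUDCA patients affected, 160 per arm: rule 10%, t-test 31%, Fisher 39%, chi-squared 53%.
- Skewed base (lognormal, log-SD 0.4): Shapiro–Wilk rejects in 100% of trials even with no toxicity. At f = 5%, rule 12%, t-test 80%, Fisher 81%.
- Fixed numbers of TUDCA patients raised by 6 SD, none on placebo: for 3, 5 and 8 patients the rule rejects in 5–6%, 7% and 11% of trials, and a t-test in 10%, 21–23% and 52%.

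**Exact p-values on counts.** Two-sided Fisher for k v 0 is 2·C(160,k)/C(320,k): 0.25 for 3 v 0, 0.06 for 5 v 0, 0.030 for 6 v 0, 0.007 for 8 v 0. Uncorrected chi-squared already passes 3.84 at 4 v 0 (320·640²/(160·160·4·316) = 4.05) with an expected count of 2 per arm, so the exact test is the fairer comparator.

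**The case against.** A reader might infer that the plan is close to blind to laboratory toxicity. The document does not support that. A marked abnormality recorded as an adverse event would appear in the per-arm tables whatever the rank test shows, and this stands. The undefined discrete safety endpoints might include counts of abnormal values; the text does not say either way. The article condenses a fuller SAP (version 2.0, named in Methods), so the absence of shift tables or graded abnormalities here is not in itself a defect.

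A reader might also infer that the switch happens only when toxicity is present. It does not: a skewed variable triggers it with no toxicity at all. Nor does the switch explain all of the low power, since with 3 or 5 patients affected the t-test alone reaches only about 10% and 21–23%.

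Two further readings are not supported. One is that the comparison is made at a late visit among survivors. Safety/harms names no visit, and withdrawals are summarised by arm elsewhere (Withdrawal/follow-up). The other is that forced vital capacity is left to this test, but the section on primary and secondary outcomes already gives it a mixed model.

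Finally, the recommended count is no cure for very small numbers: 5 v 0 gives p = 0.06, and a 1% placebo background cuts its power to 39%. That stands too, and is why the counts should be read mainly through the risk difference and its interval.

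What these objections leave untouched is the rule itself. The normality check and the move to a rank test are written in the article, and more tables elsewhere would not change what that comparison can detect.

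**Conclusion.** The point holds as a minor one. The comparison stated for laboratory and vital-sign changes has about 6% to 11% power when 2% to 5% of 160 TUDCA patients have rises of about 6 SD. At 5% affected, dropping the switch gives about 50%, and an exact test on counts gives about 79% with no placebo events or 39% with a 1% placebo background. At 10% affected the rule reaches 32% to 37% across the settings tried, so it is weak but not powerless there.

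These figures rest on assumed fractions, rise sizes, distributions, counting limit and Shapiro–Wilk level. The low power of the rank test hardly depends on the size of the rise or the shape of the base distribution; the advantage of counting does depend on the background rate. This is a better method available at low cost. It is not a contradiction in the plan or a serious error.

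**What to change.** In Safety/harms:

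1. Delete the Shapiro–Wilk check and the choice of test that hangs on it.
2. Describe mean change in each laboratory and vital-sign variable with a baseline-adjusted mixed model over all visits.
3. For each laboratory variable, report by arm, in the safety population, the number of patients with a new value beyond the laboratory's own reference limits at any post-dose visit, with risk difference, 95% CI and exact test. Do the same for vital signs with limits fixed in advance. If the discrete safety endpoints were meant to cover such counts, say so.

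The data are already scheduled at every visit (Table 1). The cost is SAP wording and a few more safety tables, to be read descriptively because no multiplicity control applies to them.

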#### Statistical software

Analyses will be carried out by the STATA 17 and R software (version 4.3.0).

## Discussion

The TUDCA-ALS incorporates the design and the experience of the previous phase II TUDCA study [5], with strengthened endpoints and the addition of innovative biomarker analysis. The responder analysis provides an innovative clinical design in ALS studies that overcomes several methodological difficulties observed in the classical parallel-group design [4]. In the earlier phase II study, responder status was defined as a minimum 15% improvement in the ALSFRS-R progression slope in the double-blind treatment phase compared to the lead-in phase. For this trial, the threshold was increased to 20%, based on suggestions received by the EMA Committee for Orphan Medicinal Products. Additionally, a supportive analysis is planned using a threshold of 25%, which was deemed clinically meaningful according to a survey conducted among experienced ALS clinical investigators [30].

The TUDCA-ALS trial, like many clinical trials worldwide, has been significantly impacted by the COVID-19 pandemic [31]. Clinical sites started recruiting patients in February 2019 across the seven involved countries, and the first patient was randomized in May 2019. The first cases of COVID-19 in Europe were registered in January 2020, with an initial outbreak in Italy and subsequent outbreaks in other European countries. The WHO declared COVID-19 a global pandemic on March 11, 2020. This unforeseen event required the prompt implementation of specific and unprecedented mitigation measures. Several interventions were implemented aimed at ensuring the completion of the trial, such as sample size reduction, introduction of telemedicine for in-person visit replacements, and the collection of information on COVID-19-related intercurrent events [9].

In the planning of sensitivity analyses, the issue of the potential impact of the pandemic on trial conduction and interpretation of results was taken into account. Special consideration is needed as some studies reported the effect of COVID-19 and of the restrictive measures on the progression of ALS [32, 33]. Moreover, persons with ALS can be at a higher risk of COVID-19 infection and its complications [34, 35]. In addition, country-specific measures were implemented to address and mitigate the COVID-19 pandemic, such as government-enforced closures, temporary cessation of study-related activities at sites, and vaccination campaigns, with differences by countries that could impact the study. Following EMA guidelines [20] and recommendations from the literature [18, 25], additional analyses were introduced to evaluate the effect of these changes on the conduct of the study and its results. Sensitivity analyses were also planned to handle missing data due to COVID-19, under different assumptions. Sensitivity analyses for the survival outcome were included, considering that the reduced sample size cannot guarantee the same power initially specified. All the proposed analyses aim to provide a full understanding and interpretation of the trial results.

